### Participant timeline

2.6

At the screening visit, the participants will be enrolled after signing a written consent form, and those who qualify per the inclusion/exclusion criteria will proceed with the trial. The detailed timeline is shown in Table 1.

**Table 1 T1:** Schedule of study.

Time point	Study period						
	Screening	Active treatment				Follow-up	
	Day 1 (visit 1)	Day 2 (visit 2)	Day 3 (visit 3)	Day 4 (visit 4)	Day 5 (visit 5)	Discharge (visit 6)	12 wks (visit 7)
Enrolment							
Eligibility screening	○						
Written informed consent	○						
Sociodemographic hic characteristics	○						
Information about accident	○						
Randomized allocation		○					
Credibility and expectancy questionnaire		○					
Intervention							
IKMT + NRT	Δ (only IKMT)	○	○	○	○	Δ (only IKMT)	
IKMT	○	○	○	○	○	○	
Assessment							
Check symptoms and Med change	○	○	○	○	○	○	○
NRS for neck pain	○	○∗	○∗	○∗	○∗	○	○
VAS for neck pain		○∗	○∗	○∗	○∗	○	
Neck ROM		○∗	○∗	○∗	○∗	○	
NRS for arm pain		○∗	○∗	○∗	○∗	○	○
VAS for arm pain		○∗	○∗	○∗	○∗	○	
NDI		○		○†		○	○
SF-12		○		○†		○	○
PGIC				○†		○	○
PCL-5-K		○		○†		○	○
Adverse events		○	○	○	○	○	○

If Day 5 (visit 5) and day of discharge are the same, then the assessment for Day 5 (visit 5) could be replaced by discharge assessment. The follow-up visit at 12 wks after registration will have a time window of ± 14 days. F/U = follow-up, IKMT = integrative Korean medicine therapy, NDI = neck disability index, NRS = numeric rating scale, NRT = non-resistance technique, PCL-5-K = post-traumatic stress disorder checklist for DSM-5, PGIC = patient global impression of change, ROM = range of motion, SF-12 = 12-item short-form health survey, VAS = visual analogue scale.

∗ Additional evaluation after treatment.

† Investigate only if Day 4 ad 5 (visit 4, 5) and day of discharge are the same.

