### Sample size

2.7

The null hypothesis of this study is that there will be no differences in the improvement of acute neck pain between the experimental group and control group after the additional use of NRT by the experimental group, and the null hypothesis will be tested using analysis of covariance as the primary analysis. The significance level (*α*) was set at 0.05 (two-tailed), type 2 error (*β*) at 0.2, and power at 90% to calculate the sample size. The sample size was determined with reference to a previous pilot study. The Cohens’ *d* was 0.63, and the correlation between the baseline and endpoint measurements was assumed to be 0.5. A total of 41 participants were needed per group. Based on a 30% potential withdrawal rate, the target number of participants was set to 60 for each group.

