### Statistical methods

2.11

In this study, both the intention-to-treat and per-protocol analyses will be performed, with intention-to-treat as the primary analysis. In the per-protocol analysis, participants who receive at least three sessions of treatment will be analyzed separately. The NRT + IKMT group and IKMT group will be compared, and the aim is to evaluate the superiority of NRT + IKMT.

Missing values will be processed through a mixed model for repeated measures in the primary analysis, and multiple imputations and the last observation carried forward will be performed for sensitivity analysis. For the Kaplan-Meier curve and log-rank test, the patients who drop out will be right censored, and regarding intermittent censoring, we will assume that no event occurred during the specified time period.

The sociodemographic characteristics of the participants and treatment expectancy will be evaluated by group. Continuous variables will be presented as mean (standard deviation) or median (quartile), and the two groups will be compared using the Student *t* test or Wilcoxon-rank sum test depending on the distribution pattern. Categorical variables will be presented as frequency (%) and will be analyzed using chi-square test or Fisher's exact test.

The endpoints of this clinical trial are the changes in the continuous outcomes (NRS, VAS, NDI, SF-12, ROM, PCL-5-K) at each time point from the baseline. A linear mixed model will be used as the primary analysis, and a random intercept model, which includes subject the random effects. Fixed effects will include baseline outcomes and clinically important covariant factors that are statistically significantly differ between groups at baseline as the covariates. In addition, time, group allocation, and the time and group interaction will be included in the model to examine the differences in the amount of change over time between the groups. For sensitivity analysis, we will perform analysis of covariance on the multiple imputations and last observation carried forward sets with the same covariates as those in the primary analysis and the group set as the fixed factor.

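### The primary mixed model gives baseline neck NRS a single slope for every reading from Day 2 to week 12; this costs almost nothing at Day 5 but can waste precision at week 12

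*Protocol article*

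**What the plan says.** Statistical methods (2.11) names a linear mixed model with a random subject intercept as the primary analysis of the continuous outcomes. On its fixed part it says: "Fixed effects will include baseline outcomes and clinically important covariant factors" (those that differ between groups at baseline), and then "time, group allocation, and the time and group interaction will be included in the model". No baseline-by-time term is listed. The same section also says that missing values in the primary analysis are handled through a mixed model for repeated measures, without naming a covariance structure.

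Table 1 schedules neck NRS on Days 1 to 5, at discharge and at 12 weeks. Days 2 to 5 carry the footnote "Additional evaluation after treatment", so each has two readings. The Abstract places the primary outcome at Day 5, immediately after treatment.

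Sample size (2.7) states that "the null hypothesis will be tested using analysis of covariance as the primary analysis". It gives a Cohen's d that "was 0.63, and the correlation between the baseline and endpoint measurements was assumed to be 0.5", and arrives at 41 per group, raised to 60 for 30% withdrawal.

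**The concern.** A baseline main effect without an interaction assumes that baseline pain predicts every later reading equally well. With the Day-2 pre-treatment score as baseline, the first later reading follows a session of about 10 minutes and the last comes some 12 weeks on. The association is likely to weaken over that span, and then one slope cannot suit all readings. Where the shared slope is too steep, chance baseline imbalance is over-corrected, and the group contrast at that reading is less precise than an analysis with its own slope would make it. Section 2.11 makes change at each time point an endpoint, so week 12 is estimated from this same model. The planned sample size, by contrast, assumes an analysis in which Day 5 has its own slope.

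**Working it through.** **1. The plan's own figure.** Inputs from 2.7: two-sided alpha 0.05, power 90%, d = 0.63, r = 0.5.

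ANCOVA: n = 2(1.960 + 1.282)² × (1 − 0.5²) / 0.63² = 39.7, so 40 per group by the normal formula and 41 by the noncentral t (power 90.2%). The stated 41 is reproduced. 41/0.7 = 58.6, so 59, against 60 stated.

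**2. Formula for the loss.** Scale all readings to unit SD, so that the reading-specific slope at time t is r_t. With a common slope b, the variance of the group contrast at t is proportional to

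1 − 2b·r_t + b² = (1 − r_t²) + (b − r_t)².

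The relative loss is (b − r_t)² / (1 − r_t²). At Day 5 the denominator is 0.75.

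- Random intercept, complete data: b is the plain mean of the r_t.
- Unstructured covariance: b = 1′S⁻¹r / 1′S⁻¹1, where S is the covariance of the readings given baseline.

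**3. Assumed inputs.** Only r = 0.5 at the endpoint is documented. The rest is assumed:

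- Day-2 pre-treatment score as baseline, followed by nine readings.
- Discharge 7 days and week 12 about 83 days after baseline; each post-treatment reading 0.02 day after its pre-treatment reading.
- Correlation at a given lag = (1 − noise) × [p + (1 − p)·exp(−lag/τ)], with persistent share p from 0 to 0.4, reading noise from 5% to 30%, and τ set so that Day 5 gives 0.5.

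**4. One case in full** (p = 0, noise 5%, random intercept). The nine correlations are 0.95, 0.77, 0.76, 0.62, 0.62, 0.50, 0.50, 0.21 and 0.00, with mean b = 0.548.

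- Day 5: (0.548 − 0.50)² / 0.75 = 0.3%.
- Week 12: 0.548² / 1 = 30%.

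**5. Selected cases** (power by noncentral t at 41 per group).

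| p | noise | random intercept: b | Day 5 | power | week 12 | unstructured: b | Day 5 | power | week 12 |
|---|---|---|---|---|---|---|---|---|---|
| 0 | 5% | 0.55 | +0.3% | 90.1% | +30% | 0.79 | +11.6% | 86.9% | +63% |
| 0 | 30% | 0.49 | +0.0% | 90.2% | +24% | 0.46 | +0.3% | 90.1% | +21% |
| 0.4 | 5% | 0.59 | +1.1% | 89.9% | +5% | 0.85 | +16.3% | 85.5% | +26% |
| 0.4 | 30% | 0.52 | +0.1% | 90.2% | +6% | 0.54 | +0.2% | 90.2% | +7% |

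Over the whole grid, the random-intercept loss is about 0-1% at Day 5 and 5-30% at week 12. The unstructured loss is about 0-16% at Day 5 and 7-63% at week 12. If the correlation did not fade at all, there would be no loss anywhere.

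**6. Cross-checks.** A freely drawn steep profile (0.90, 0.80, 0.75, 0.70, 0.65, 0.60, 0.50, 0.40, 0.10; mean 0.60) gives +1.3% at Day 5 and +25% at week 12. A simulation of 20,000 trials gave variance ratios of 1.01 and 1.25 with no bias. A harsher profile running from 0.95 to 0 gives +2.5% and +41%. Losing two points of power at Day 5 needs a slope gap of about 0.23; the largest gap in these freely drawn random-intercept profiles is 0.14.

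**The case against.** A reader might infer that the trial fails to obtain the Day-5 precision behind 41 per group. The documents do not support that. Section 2.11 names a random intercept, and under it Day 5 lies near the middle of the range of slopes, so the shared slope stays close to its own. The larger losses need an unstructured covariance that the article never specifies; the repeated-measures wording appears only in the sentence on missing values. They also need very low reading noise: at 20-30% noise even the unstructured Day-5 loss is at most about 2%. Nor is 41 tied to ANCOVA alone. Section 2.7 gives both a type 2 error and a power ("at 0.2, and power at 90% to calculate the sample size"), and these contradict each other. An unadjusted t-test at 80% power also needs 41 per group.

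Further points stand in part. A common baseline slope is a valid specification, and week 12 is not the primary time point. Table 1 has no week-12 VAS or ROM, so the week-12 argument does not reach those outcomes. The planned ANCOVA sensitivity analyses estimate a slope of their own when run at a single time point, but they use imputed and carried-forward sets and do not replace the primary model.

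It can also be said that such a detail belongs in an analysis plan that is not shown. The article, however, writes out the fixed effects and the one interaction it wants, so a plan that followed it would have no baseline-by-time term.

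**Conclusion.** The point holds as a minor efficiency improvement. The listed fixed effects give baseline one slope for all readings. At the Day-5 primary contrast under the named random-intercept model this costs about 0-1% of variance, with power at 41 per group of 89.9-90.2%, so neither the primary comparison nor the sample size is undermined. At week 12 the loss is about 5-30% of variance if the baseline association fades. These sizes assume equal SDs, complete data, the Day-2 pre-treatment score as baseline, all nine later readings in one model, and correlations that the article does not give. Under randomization with complete data the common slope causes no bias.

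**What to change.** In Statistical methods (2.11), add a baseline-by-time interaction, with time as a categorical factor, to the mixed models for outcomes that have a baseline and repeated later readings. Each reading then has its own baseline slope, and the Day-5 contrast is adjusted as in the ANCOVA of 2.7 whichever covariance structure is used. For neck NRS this means nine slopes in place of one, so about eight extra parameters. It needs no new data, patients or visits.

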### Data monitoring

2.12

We will monitor the data to ensure participants’ safety and the integrity of the study data. During monitoring, case records and evidence documents will be compared, and participants’ safety data will be reviewed. The initial monitoring will be performed during participant screening and enrolment, and at least two rounds of monitoring will be performed during the study period. The number of monitoring rounds can be adjusted upon discussion among the investigators. Interim analysis will not be performed during this clinical trial.

### Ethics and dissemination

2.13

The study protocol, case report form, and informed consent form will be submitted to the Institutional Review Board, and the study will be initiated once it is approved. An amendment of the documents will be approved by the Institutional Review Board in advance, and the documents will be continuously updated. All participating investigators will undergo clinical trials and relevant training and will familiarize themselves with the protocol and SOP. Prior to beginning the trial, the investigators will provide the participants with an information sheet outlining the purpose of the study, timeline, and information to be collected to obtain their informed consent, and a copy of the information sheet will be provided to the participants.

### Informed consent

2.14

Before the start of the study, the researcher will provide the patients with appropriate information about the study for a sufficient time and fills out the study consent form. The signed consent form of the researcher and the participant is kept by the researcher and a copy is provided to each participant.

### Confidentiality

2.15

All personal data of the participants will be managed rigorously per the Personal Information Protection Act, and all data collected from the consenting participants will be processed anonymously. If the study data are provided to any third organization for professional data analysis, the data will be de-identified and given arbitrary identification codes. All information regarding this clinical trial, including participants’ personal information, will be retained for 3 years following the completion of the study, after which they will be discarded in accordance with the established protocol.

### Ancillary and posttrial care

2.16

Participants can contact the sub-investigator at any time regarding a study-related injury or for other medical purposes using the contact information provided in advance. If a participant develops an injury directly due to the study procedure, we will provide the best medical interventions and compensation per the designated trial-related insurance.

## Discussion

3

NRT can enhance impaired functions and alleviate pain in patients with acute neck pain caused by a TA by helping them overcome the fear of pain and movement and retraining them using muscle stabilization and coordination.^[23,24]^ Technically, NRT is a technique that combines joint mobilization and pressure release techniques. Mobilization is effective for the whiplash syndrome, which is characterized by impaired cervical flexor and extensor functions due to neck injury and pain caused by acceleration and deceleration of a vehicle.^[25]^ Mealy et al reported that patients with a whiplash injury who underwent repetitive and passive movements within tolerable ranges had better outcomes than had their counterparts who simply rested or had cervical braces for the first 2 weeks. These authors utilized small movements within limited amplitudes, with smaller amplitudes for spasms and larger amplitudes for stiffness.^[12]^ A pressure release technique is a common technique used in manual therapy, and Pecos-Martin et al improved the pressure pain threshold and strength of the levator scapulae by applying 60 to 90 seconds of pressure on nuchal muscles.^[8]^

One limitation of this study is that the participants and physicians administering the intervention cannot be blinded due to the nature of the intervention. To address this issue, the assessor will be blinded. This RCT aims to evaluate the effectiveness of NRT in a real-world clinical setting. Considering that the target patient population is patients hospitalized after a TA and that these patients are generally treated through IKMT comprising acupuncture, Chuna therapy, pharmacopuncture, and herbal medicine, we used an add-on design for the interventions, where the control group will receive an IKMT while the experimental group will receive NRT in addition to IKMT. Further, to enroll patients with acute neck pain, we included TA within the past week as one of the inclusion criteria. Helping patients act normally by controlling their pain and fear would facilitate early recovery from residual pain.^[4]^

This study will shed light on the effectiveness and safety of early NRT on acute neck pain caused by a TA. Preventing the chronic progression of pain by effectively reducing pain in early stages will ensure the quick return of patients to their normal lives.^[26]^ Consequently, NRT will be one of the viable treatment options for patients involved in a TA, which will present practical benefits for healthcare-related policy makers and clinicians.
